## **25.Data management and monitoring**

Data processing software such as GraphPad Prism, Excel, and Word will be utilized. Data collection and management will be conducted through Microsoft Excel by trained research assistants who are responsible for data entry and organization. All data will be regularly backed up and stored in encrypted form to ensure security. During analysis, statistical software will be used to process the data from Excel to evaluate the effects of the intervention. Data management and monitoring follows national and international standards of good clinical practice and complies with regulatory and ethical requirements. All relevant or irrelevant serious adverse events affecting patients will be collected and documented in source files. The quality of the study and regulatory compliance will be continuously monitored. Monitors will not be involved in the conduct of the study to ensure objectivity and independence. The Ethics Committee has approved the monitoring of the study to verify the qualifications of the investigators and study team members and to ensure the soundness and appropriateness of the documentation. In addition, data quality monitoring will be conducted through a variety of means to ensure accuracy, completeness and consistency of data.

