## **6. Research Content**

This study was a single-center, randomized, controlled clinical trial protocol planned to include 76 patients with SAP who were randomly divided into two groups in order to assess the efficacy and safety of different SMT-based nurse-led epidural analgesia delivery modalities. In the control group, continuous TEA was used with a combination of nalbuphine 40 mg, ropivacaine 225 mg, lidocaine 0.2 g, and 0.9% saline 6 ml in a total of 50 ml, which was pumped at a rapid duration of 3-5 ml/h. When the patient's VAS-P exceeded 3 points or when the patient was unable to tolerate pain, the pumping of the combined solution was appropriately adjusted upward by 1-2 ml/h. In the experimental group, on the basis of continuous TEA, a pain management nurse led the TEA pain management strategy according to the SMT, reported to the doctor when the VAS-P exceeded 3 points or when the patient was unable to tolerate pain, and injected 5 ml of the combined drug solution intermittently with an intermittent interval time of greater than 2 hours each time, as per the doctor's prescription. Hours. The patient's pain response and feedback were also continuously monitored for timely adjustment of analgesic measures. The primary outcome indicator was VAS-P, and secondary outcome indicators included intra-abdominal pressure(IAP), number of additional interventions(NAI), dosage of combined drugs(DCD) , number of days of epidural placement(NDEP), and 16 adverse events(AE). Outcome indicators included puncture success rate(PSR), length of stay in ICU (ICU-LOS), 28-day mortality rate (28D-MR), and patient satisfaction score for analgesic effect(SAE).

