## **7.Study Hypothesis**

(1) The experimental group will be superior to the control group in terms of VAS-P reduction and IAP control,

suggesting that intermittent epidural injections provide superior pain management and visceral protection.

(2) The incidence of adverse events in the experimental group will not be higher than that in the control group, and the length of hospitalization in the ICU and 28-day mortality will be lower, suggesting that the intermittent injection method is safe and may improve prognosis.

(3) Analgesic satisfaction scores will be higher in the experimental group than in the control group, suggesting that the nurse-led pain management program is more responsive to patient needs.

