## **21.Adverse Events**

Puncture-related AE : Healthcare workers observe and record the following 8 indicators during daily care and examination: spinal cord and nerve root injury, epidural hematoma, puncture site infection, total spinal anesthesia, headache after dural puncture, intradural infection, catheter blockage, catheter breakage and ectasia. The number of cases of AE was counted for the period of epidural placement.

Drug-related AE: Pain management nurses observed and recorded the following 8 indicators after the patient's medication: anaphylaxis, hypotension, nausea/vomiting, itching, tremor, sensory disturbances in the lower limbs, fever, decreased oxygen saturation, bradycardia or tachycardia. The statistical methods and times were the same as those for puncture-related AE.

22.Outcome Indicators

Puncture surgery rate (PSR): Calculate the ratio of the number of successful puncture cases to the total number of punctures, which was counted by the data collector.

Length of stay in ICU (ICU-LOS): when patients are transferred out of ICU, the total number of days of ICU stay is recorded.

28-day mortality rate (28D-MR): count the number of patients who died within 28 days and calculate the 28-day mortality rate.

Satisfaction with analgesic effect (SAE): patients' satisfaction with the analgesic effect was assessed using a 0-10 scale, with 0 indicating very dissatisfied and 10 indicating very satisfied. It was collected by the data collector on the day of epidural tube removal.The intervention and data collection process are shown in [Figure 4](#).

[figure not shown]

Figure 5: Intervention and Data Collection Process

23. Quality control

(1) All staff must undergo standardized training and pass assessments to ensure consistent implementation of the intervention, minimizing both executor and assessor bias.

(2) Collected data will be cross-verified by two researchers before being entered into the system to ensure data accuracy.

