#### **24.Data analysis**

Data will be analyzed in this study using GraphPad Prism software to ensure accuracy and consistency of results. For baseline characteristics data, patients' age, gender, admission time, and disease-related clinical information will be descriptive statistics, Categorical variables will be presented as frequencies and proportions, whereas normally distributed continuous variables will be described using means and standard deviations. For non-normally distributed data, descriptive statistics will utilize median and percentile values (P25 and P75). Between-group comparisons will be carried out using t-tests, analysis of variance, chi-square tests, Mann-Whitney U tests, and statistical methods for repeated measures data to assess differences among the groups. The significance level in this study will be set at  $\alpha=0.05$ , with  $P<0.05$  indicating statistical significance.

The changes in the primary outcome indicator VAS-P at different time points (0h, 1h, 6h, 12h, 24h, 48h, 72h) will be assessed by repeated measures analysis of variance (ANOVA) if the data conform to a normal distribution. Secondary outcome indicators, such as intra-abdominal pressure (IAP), will be analyzed in the same manner. The number of additional interventions (NAI) and the dose of coadministered medication (DCD) will be expressed as mean  $\pm$  SD or median (IQR), and comparisons between groups will be made using the t-test or the Mann-Whitney test. The number of days of epidural placement (NDEP) will also be subjected to descriptive statistics and between-group comparisons. The number of cases of adverse events (AE) will be expressed as frequency, and comparisons between groups will be made using the chi-square test or Fisher's exact test. The outcome indicators, including puncture success rate (PSR), length of stay in the ICU (ICU-LOS), 28-day mortality rate (28D-MR), and satisfaction with analgesic effect score (SAE), will be subjected to descriptive statistics and between-group comparisons using the chi-square test or Fisher's exact test, as well as the t-test or the Mann-Whitney test.

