## **29. Risks and Safety Measures of This Study**

### **(1) Clear Notification of Reasonable Anticipated Risks or Inconveniences to Subjects:**

In this study, subjects may face the following risks or inconveniences, including procedural risks (such as failed puncture, epidural hematoma, nerve injury, etc.), management risks (such as poor communication, coordination difficulties, non-standard data management, etc.), medication risks (such as incorrect drug dosage, drug allergic reactions, drug interactions, etc.), and poor patient compliance risks (patients may not cooperate with the study procedures or may drop out of the study midway due to pain, discomfort, or other reasons).

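### The adverse-event comparison is a closed list counted only during catheter placement, so non-fatal serious events outside that list or window have no stated route to a comparison by arm

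*Protocol*

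**What the plan says.** Four parts of the protocol bear on this.

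- **Collection.** Section 25 states: "All relevant or irrelevant serious adverse events affecting patients will be collected and documented in source files". It names no other destination. The same section says "During analysis, statistical software will be used to process the data from Excel to evaluate the effects of the intervention".
- **Outcome definition.** Section 6 gives the secondary outcomes as including "number of days of epidural placement(NDEP), and 16 adverse events(AE"). Section 21 itemises them in a puncture-related list ("Healthcare workers observe and record the following 8 indicators during daily care and examination") and a drug-related list, also stated to hold 8. Cases are counted for the time the catheter is in place, and the drug-related list uses the same timing.
- **Analysis.** Section 24 says "The number of cases of adverse events (AE) will be expressed as frequency", with a chi-square or Fisher's exact test between groups. It names no summary of serious adverse events. The abbreviation SAE in that section means satisfaction with analgesic effect.
- **Use of the result.** Hypothesis 2 in section 7 expects that "The incidence of adverse events in the experimental group will not be higher than that in the control group". Together with shorter ICU stay and lower 28-day mortality, it takes this to suggest that the injection method is safe.

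**The concern.** The protocol collects harms broadly and compares them narrowly. Serious events are gathered whatever their cause, but the outcome that supports the safety statement is a fixed list with a fixed window. A serious non-fatal event of a type not listed, or a listed event that appears after the catheter is removed, would be known to the investigators and could still be absent from the comparison.

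The experimental arm adds 5 ml injections of a three-drug solution to the continuous infusion, so an excess of harm in that arm is what the safety analysis must be able to show. If the excess fell outside the list or window, the adverse-event result would look the same as if it had not happened. The primary pain outcome is not affected.

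**Working it through.** **1. The stated count.** Section 6 says 16, and section 21 says 8 and 8, which agrees. Counting the comma-separated items in section 21:

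- Puncture-related: cord or nerve-root injury; hematoma; site infection; total spinal; post-puncture headache; intradural infection; blocked catheter; broken or displaced catheter. Total 8.
- Drug-related: anaphylaxis; low blood pressure; nausea or vomiting; itch; tremor; altered leg sensation; fever; desaturation; slow or fast heart rate. Total 9.

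8 + 9 = 17, so the stated 16 does not match its own list.

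**2. Following each kind of serious event through the text.**

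| Serious event | Collected (section 25) | In an arm comparison (section 24) |
|---|---|---|
| Fatal, within 28 days, any cause | Yes | Yes, through 28-day mortality |
| Non-fatal, listed, during placement | Yes | Yes, as an adverse event |
| Non-fatal, listed, after catheter removal | Yes | No stated route |
| Non-fatal, not listed, at any time | Yes | No stated route |

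The last two rows are the gap. Section I gives examples of unlisted events: delirium, somnolence and myoclonus as opioid effects (written there of intravenous use; the epidural solution contains nalbuphine), and renal failure as a consequence of the disease.

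**3. Dosing errors and interactions.** Section 29 names "medication risks (such as incorrect drug dosage, drug allergic reactions, drug interactions, etc".). Of these, allergy has a matching item (anaphylaxis). The other two are causes rather than events. Several likely consequences are listed: hypotension, desaturation, bradycardia or tachycardia, and total spinal anesthesia. What the outcome lacks is a count of the errors or interactions themselves, and of any consequence that is not listed.

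**4. How likely such events are.** The protocol gives no rates, so these are assumptions. With 76/2 = 38 patients per arm, the chance of at least one event in an arm is 1 − (1 − p)^38:

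- p = 0.02: 1 − 0.98^38 = 0.536
- p = 0.05: 1 − 0.95^38 = 0.858
- p = 0.10: 1 − 0.90^38 = 0.982

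**5. What a comparison could show.** With 38 per arm and none in the control arm, Fisher's exact two-sided p is 0.054 for 5 events against 0, and 0.025 for 6 against 0. If disease-driven serious events reached an assumed 40% in each arm, the approximate 95% interval for the risk difference would be ±1.96 × √(2 × 0.40 × 0.60 / 38) = ±0.22, or 22 percentage points.

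**The case against.** The strongest reply is that open collection of serious events beside a list of solicited events is a coherent design, and that tabulation of serious events normally sits in a statistical analysis plan, which is not shown. The layout of such a table could indeed be left there. But the protocol is not silent on the outcome: it fixes the list, the window and the test. An analysis plan also cannot tabulate events that never reach the analysed dataset.

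A reader might infer that serious events go only to source files and never reach an arm comparison. The text does not support that. Section 25 does not exclude entry in Excel; section 9 makes the data collectors responsible for adverse events without limiting them to the list; the sentence in section 24 is not expressly confined to the list; and all deaths to day 28 are compared. Other recording and review routes exist: a reporting system for operation-related events (section 29), recording of adverse reactions (section 32) and safety committee review mid-study and at the end (section 33). None of these three is a between-arm result.

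A reader might also infer that the gravest harms, or the effects of dosing errors, escape altogether. That too goes too far: cord injury, epidural hematoma, total spinal anesthesia, intradural infection and anaphylaxis are listed, as are many consequences of dosing errors. Total drug dose and additional interventions are also compared by arm.

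Finally, the probabilities above rest on assumed rates and say nothing about a difference between arms. That objection stands.

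**Conclusion.** The point holds in a limited form. Followed as written, the adverse-event comparison covers a closed list during catheter placement. Non-fatal serious events outside that list or window are collected but have no stated path to the analysed data or to a comparison by arm. This narrows what the safety part of hypothesis 2 can support; it does not make the safety data empty and does not touch the primary result. The conclusion assumes that adverse events in section 24 means the outcome defined in sections 6 and 21, the only definition the protocol gives.

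The size cannot be fixed from the protocol. At assumed incidences of 2% to 10%, the chance of at least one such event in an arm runs from 54% to 98%. That makes the gap a practical one, but is no evidence of an imbalance. Separately, the stated 16 events and the 17 itemised must be reconciled.

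**What to change.** - **Section 25:** state that the serious adverse events already collected are entered in the study dataset as well as the source files.
- **Section 24:** report the number of patients with at least one serious adverse event, by arm as randomised, over the follow-up already in the section 35 schedule (to ICU transfer or day 28), with a risk difference, an exact 95% confidence interval and a line listing. No new causality adjudication is needed.
- **Section 7, hypothesis 2:** base the safety statement on this table together with the listed events.
- **Sections 6 and 21:** reconcile the count of 16 with the 17 items.

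The cost is a few sentences, a dataset field, a table and a listing, with some extra data entry. Keeping to the existing follow-up avoids new visits after the ICU. The drawback is imprecision: serious events due to pancreatitis itself will occur in both arms, and with 38 per arm the interval will be wide. The table should therefore be read as an estimate and not as proof of equal safety.

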## **26. Innovation:**

This study is the first to explore the application of Symptom Management Theory (SMT) in epidural analgesia for patients with severe acute pancreatitis (SAP) led by nurses. Integrating SMT into pain management provides a structured approach for symptom assessment and intervention, which may enhance the effectiveness of pain control. The study also introduces a flexible analgesic regimen that combines continuous thoracic epidural analgesia (TEA) with intermittent injections on demand, aiming to offer more personalized and effective pain management. These innovative aspects may provide new insights for optimizing pain management plans for SAP patients and promote the role of nurses in pain management as well as the application of SMT in other clinical settings.

## **27. Limitations:**

This study is a single-center trial, which may limit the generalizability of the study results. Although the sample size calculation ensures statistical power, it may still be insufficient to detect small but clinically significant

differences. Additionally, the study relies on the accurate assessment of pain using the Visual Analog Scale for Pain (VAS-P), which may be subject to patient subjective interpretation. There may also be data missing due to patient withdrawal or other unforeseen circumstances, which could affect the robustness of the results. Furthermore, the study duration may not be long enough to fully capture the long-term effects of the intervention.

## **28. Practical Significance:**

Despite the limitations, this study holds significant practical value. By exploring the potential benefits of nurse-led pain management based on SMT, it paves the way for providing more personalized and effective pain management strategies for SAP patients. If the experimental group shows superior outcomes, this could lead to a shift in clinical practice, favoring intermittent epidural injections over continuous TEA. This would not only enhance patient comfort and satisfaction but also potentially reduce healthcare costs associated with prolonged ICU stays and adverse events. The study results may also encourage further exploration of the role of nurses in pain management and the application of SMT in other clinical settings.

## **29. Risks and Safety Measures of This Study**

### **(1) Clear Notification of Reasonable Anticipated Risks or Inconveniences to Subjects:**

In this study, subjects may face the following risks or inconveniences, including procedural risks (such as failed puncture, epidural hematoma, nerve injury, etc.), management risks (such as poor communication, coordination difficulties, non-standard data management, etc.), medication risks (such as incorrect drug dosage, drug allergic reactions, drug interactions, etc.), and poor patient compliance risks (patients may not cooperate with the study procedures or may drop out of the study midway due to pain, discomfort, or other reasons).

### **(2) Safety Measures to Be Taken in This Study:**

**Procedural Risk Management:** The thoracic epidural puncture and catheter placement will be performed by experienced doctors to increase the success rate of puncture; medications will be used reasonably. Regular training and assessment of the puncture and medication administration procedures will be conducted for the medical staff involved in the study to ensure the proficiency and standardization of the operations; during the operation, the vital signs and reactions of the patients will be closely monitored, and the operation will be immediately stopped and corresponding measures taken if any abnormalities occur; a system for reporting adverse events will be established to promptly record and report adverse events related to the operation, and to conduct cause analysis and develop improvement measures.

**Management Risk Management:** An interdisciplinary research team will be established to clarify the responsibilities and tasks of each member, regular team meetings will be held to communicate and solve problems

that arise during the study in a timely manner; detailed research procedures and operating standards will be formulated to ensure that every link of the study is regulated and to reduce problems caused by chaotic management; a dedicated person will be assigned to manage the collection, entry, and management of data, with regular data backups and quality checks to ensure the integrity and accuracy of the data; a complete patient follow-up mechanism will be established to ensure that patients receive timely follow-up and necessary medical support during and after the study.

**Medication Risk Management:** Strict adherence to drug preparation and administration standards will be ensured to guarantee accurate drug dosages; clearly labeled drug containers will be used to avoid drug confusion; before using new drugs or drug combinations, patients' allergy histories will be inquired about and necessary allergy tests will be conducted, with antiallergic drugs and emergency equipment prepared to immediately handle any allergic reactions; during drug administration, the vital signs and reactions of patients will be closely monitored, and drug administration will be immediately stopped and corresponding measures taken if any abnormalities occur; training on drug knowledge and administration procedures will be provided to the medical staff involved in the study to ensure their familiarity with the pharmacological actions, adverse reactions, and handling methods of the drugs.

**Poor Patient Compliance Risk Management:** Before the start of the study, the purpose, methods, potential risks, and expected benefits of the study will be explained in detail to patients and their families to ensure their full understanding and signing of the informed consent form; during the study, regular communication with patients will be maintained to understand their feelings and needs and to answer questions in a timely manner; the pain management plan will be optimized to ensure effective pain relief for patients during the study, and the doses and administration methods of analgesic drugs will be adjusted in a timely manner based on patient feedback to improve patient comfort and compliance.

### **30. Rights, Benefits, and Compensation of Subjects Participating in This Study**

#### **(1) Informed Consent Acquisition:**

The researchers will provide subjects with a detailed introduction to the research arrangements of the scientific research project. Participation is entirely voluntary, and researchers will report all events related to the subjects to enable them to decide at any time whether to continue participating.

#### **(2) Benefits:**

This study aims to compare the analgesic effects of different epidural medication methods on patients with severe acute pancreatitis (SAP), in order to provide new directions and theoretical support for the treatment of SAP patients, as well as to select the best epidural medication for SAP patients. This can help shorten the length of stay

in the ICU for patients, reduce medical costs, and alleviate the economic burden on patients.

(3) Compensation:None.

(4) Medical Care and Protection of Subjects in This Study:

This study will fully ensure the medical care and rights of subjects. Subjects may face the following risks:

**Procedural Risks:** Although epidural puncture and drug administration procedures are routinely performed in the department, there may still be procedural risks, such as failed puncture, epidural hematoma, nerve injury, etc. The sources of risk include procedural techniques, individual differences among patients, equipment failure, etc. The emergency plan includes personnel training, monitoring and handling, and reporting system.

**Management Risks:**The study involves interdisciplinary collaboration and complex management processes, and there may be problems such as poor communication, coordination difficulties, and non-standard data management. The sources of risk include interdisciplinary collaboration, data collection and management, patient follow-up, etc. The emergency plan includes establishing an interdisciplinary research team, optimizing processes, data management, and patient follow-up.

**Medication Risks:** Epidural drug administration involves the use of multiple drugs, and there may be risks such as incorrect drug dosage, drug allergic reactions, drug interactions, etc. The sources of risk include drug preparation, drug dosage, individual differences among patients, etc. The emergency plan includes drug management, allergy prevention, monitoring and handling, and drug training.

**Poor Patient Compliance Risks:** Patients may not cooperate with the study procedures or may drop out of the study midway due to pain, discomfort, or other reasons, which may affect the integrity of the study and the reliability of the results. The sources of risk include individual differences among patients, pain management effectiveness, and poor communication. The emergency plan includes communication and education, pain management.

